### Injury-Preventive Behavior

As the intervention developed by Adriaensens et al (Dutch Consumer Safety Institute) [10] was effective in promoting injury-preventive behavior but was time-consuming, the research team wanted to develop an intervention to stimulate injury-preventive behavior among novice runners without the associated time burden. In this study, injury-preventive behavior is defined as follows: (1) using a (personalized) training schedule: use of a training schedule that fits the physical condition of the athlete and represents a realistic running goal was proposed by running experts as an important factor in preventing running injuries; (2) performing strength and technique exercises [12] to improve the amount of force that can be exerted on the body while running; and (3) performing an active warm-up prior to running [13]. Each of these injury-preventive behaviors is divided into preparatory acts, such as searching for information about strength exercises and structural injury-preventive measures like performing strength exercises. All injury-preventive behaviors are assessed through single questions (yes, no, or not applicable).

### Procedures

Upon enrollment, participants will be asked to report the injury-preventive measures they usually take before or during their running activities. Participants’ demographic characteristics, including their contact email address, sex, age, running experience, running motivation, physical fitness, current injuries and physical complaints, and injury-preventive measures, will also be collected upon enrollment via a Web-based enrollment questionnaire (Table 1).

**Table 1 table1:** Overview of research topics per questionnaire in this study.

Research topics	Enrollment questionnaire	At 1 month after enrollment	At 3 months after enrollment	At 5 months after enrollment
Age	Present	N/A^a^	N/A	N/A
Sex	Present	N/A	N/A	N/A
Sports participation other than running	Present	Absent	Absent	Absent
Running motivation	Present	Absent	Absent	Absent
Running experience (in months or years)	Present	Absent	Absent	Absent
Level of running (novice, seminovice, experienced, etc)	Present	Absent	Absent	Absent
Running frequency per week	Present	Present	Present	Present
Physical fitness	Present	Present	Present	Present
Risk perception	Present	Present	Present	Present
Injury-preventive behavior	Present	Present	Present	Present
Running-related injuries	Present	Present	Present	Present
Physical complaints	Present	Present	Present	Present

^a^N/A: not applicable.

All personal information and contact information from the participants will be handled by the principal researcher. This researcher will export the data from SurveyMonkey and store it in a password-protected drive. Participant names will be replaced with numbers and stored as reidentifiable data. The data with participant numbers will be utilized in the statistical analyses. Upon the conclusion of the data collection period, the questionnaire and associated responses will be deleted from SurveyMonkey.

Questionnaires will be administered at study commencement and at 1, 3, and 5 months post-commencement. In these follow-up questionnaires, participants will be asked to retrospectively report in detail what they have done in the past month(s) regarding injury prevention during their running activities and will be asked questions about their current injury-preventive behavior, running activities, and running injuries during running activities. The injury definition utilized in this study is “any physical complaint arising during a running activity that does not allow the participant to complete the activity or affects their ability to participate in future running activity” [14-17].

At 4 time points, a Web-based questionnaire will be sent by email to participants by the principal researcher, using the Web-based questionnaire system SurveyMonkey. When participants fail to complete a questionnaire, reminder notifications will be sent via email by the principal researcher using the Web-based questionnaire system SurveyMonkey 7 days after a questionnaire is due. A second reminder will be sent after 2 weeks.

The evaluation of the effectiveness of RunFitCheck will not take place in an experimental setting. Participants in the intervention group will be given access to the intervention, but no further conditions will be applied to the use of the intervention. In the questionnaires at 1, 3, and 5 months, the intervention group will be asked about their use of the intervention, attractiveness of the intervention, behavioral actions they take after being exposed to the intervention, their intention to use this intervention again, and how they would want to be informed about this intervention. If participants indicate they do not use the intervention, they will be asked to give detailed information about why they do not use the intervention.

### Statistical Analysis

Descriptive analyses (mean [SD], frequency, and range) will be conducted for the different baseline variables in both study groups. To evaluate the success of the randomization, baseline variables will be analyzed for differences between the intervention and control group (chi-square test, independent *t* test, and Mann-Whitney test).

Relative risks (RRs) and a 95% CI will be used to analyze behavioral change according to the intention-to-treat analyses: (1) using a (personalized) training schedule, (2) performing strength and technique exercises, (3) performing a warm-up. Participants who do not execute a certain injury-preventive measure at study commencement will be selected for analysis, since among these participants, most behavioral change can be expected. If there are any differences in descriptive characteristics at baseline (eg, differences in sex, age, or running experience), subanalyses for sex, different age categories, etc will be performed.

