
## Methods

### Objective and Hypothesis

The objective of the study is to evaluate the effectiveness of the developed RunFitCheck intervention (in Dutch) to promote injury-preventive behavior among novice runners. The hypothesis in this study is that the developed intervention will lead to 10% difference in favorable injury-preventive behavior in the intervention group compared with the control group.

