### Sample Size and Allocation

In this study, the aim is to increase injury-preventive behavior by 10% in the intervention group. In previous literature, 12.6% increase in injury-preventive behavior (in this case, the inclusion of a warm-up) was found during a 3-month intervention [10]. To achieve 80% power with a significance level of.05, the sample size calculation revealed that 384 participants per study group are needed in this study. Taking into account a response rate of 85% and a dropout rate of 10% over the 5-month follow-up period, a total of 1000 participants will be approached in this study. Eligible participants will be simultaneously allocated at random to the intervention or control group after study commencement, using a computerized random number generator (the Aselect function in Excel). No restrictions will be imposed for the allocation; simple randomization will be performed. All steps in the randomization process will be done by the principal researcher.

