### Injury-Preventive Behavior

As the intervention developed by Adriaensens et al (Dutch Consumer Safety Institute) [10] was effective in promoting injury-preventive behavior but time-consuming, the Dutch Consumer Safety Institute wants to develop an intervention to stimulate injury-preventive behavior among novice runners without the associated time burden. Therefore, injury-preventive behavior as a primary outcome in our study instead of the more traditional RRIs was chosen. It is well known that people find it difficult to change health-related behavior. Sustaining lasting change in health-related behavior is a detailed and lengthy process [18]. Our study assesses a small part of this process, focusing on a 10% change in injury-preventive behavior as an indication that the intervention is efficacious.

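### One hypothesis and one single-test sample size, but three behaviours analysed separately, with no primary behaviour, time point or success rule fixed

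*Protocol article*

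**What the plan says.** All references are to the protocol article.

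- **Objective and Hypothesis** gives one hypothesis: "the developed intervention will lead to 10% difference in favorable injury-preventive behavior in the intervention group compared with the control group".
- **Sample Size and Allocation** gives one calculation: "To achieve 80% power with a significance level of.05", it finds that "384 participants per study group are needed in this study". The only reference figure is for one behaviour: "12.6% increase in injury-preventive behavior (in this case, the inclusion of a warm-up) was found during a 3-month intervention". No control-group rate is given.
- **Injury-Preventive Behavior (Methods)** defines the outcome as three behaviours and adds: "Each of these injury-preventive behaviors is divided into preparatory acts", as opposed to structural measures.
- **Procedures** (with Table 1) collects behaviour at 1, 3 and 5 months. Each follow-up asks about "what they have done in the past month(s) regarding injury prevention during their running activities" and also about current behaviour.
- **Statistical Analysis** plans relative risks with 95% CIs for "1) using a (personalized) training schedule, (2) performing strength and technique exercises, (3) performing a warm-up". Each is analysed among participants not doing that behaviour at baseline. No time point, composite, threshold or multiplicity rule is given.
- **Injury-Preventive Behavior (Discussion)** makes injury-preventive behaviour the primary outcome and describes the study as "focusing on a 10% change in injury-preventive behavior as an indication that the intervention is efficacious".

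**The concern.** The hypothesis, the power calculation and the efficacy claim are all singular, while the analysis is plural. Nothing in the article links the three results, or the follow-up waves, to the one claim. Each behaviour also has its own analysis set, so no single population yields one result for injury-preventive behaviour.

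If any favourable interval can support the claim, the false-positive risk exceeds that of the single test on which the trial was sized. An early effect at 1 month could also stand in for a sustained one at 5 months. If the claim is instead protected by an adjustment, or by requiring all three behaviours to succeed, the stated 80% power no longer describes it.

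**Working it through.** **1. Reproduce the 384.** Stated inputs: alpha .05, power 80%, difference 10%. Assumptions: two-sided test, 10 percentage points, equal groups, control rate 40% or 50%.

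Unpooled formula: n = (z₁₋α/₂ + z₁₋β)² × [p₁(1−p₁) + p₂(1−p₂)] / (p₁−p₂)²

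- With z values 1.96 and 0.84: (1.96 + 0.84)² × (0.24 + 0.25) / 0.01 = 7.84 × 49 = 384.2 per group. Unrounded z values give 384.6.
- The pooled version gives 388 at the same rates, and 376 to 392 for control rates from 35% to 55%.
- One-sided versions (about 303-309 near these rates) and continuity-corrected versions (about 404-412) do not match.
- Inflation: 768 / (0.85 × 0.90) = 1004, against the stated 1000.

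The stated size is therefore that of one two-sided .05 comparison.

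**2. Chance of at least one false result when the intervention has no effect.** Each 95% CI excludes 1 in the favourable direction with probability 2.5%, and in either direction with probability 5%.

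| Comparisons | Favourable | Either direction |
|---|---|---|
| 1 | 2.5% | 5% |
| 3 (one time point), independent | 1 − 0.975³ = 7.3% | 1 − 0.95³ = 14.3% |
| 9 (three time points), independent | 1 − 0.975⁹ = 20.4% | 1 − 0.95⁹ = 37.0% |
| 9, correlated (simulated) | about 11-19% | about 22-35% |

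The last row uses 200,000 draws per setting of nine correlated normal statistics. The same behaviour at different times correlates 0.3 to 0.9; different behaviours correlate 0 to 0.3. These correlations are assumptions, as the article gives none. Raising the between-behaviour correlation to 0.5 lowers the bottom of each range to about 10% and 20%. For three comparisons, a between-behaviour correlation of 0.5 gives 6.3% favourable and 12.5% in either direction.

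**3. Power at 384 per group with Bonferroni over three behaviours** (alpha .05/3 = .0167; also the first Holm step).

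| Assumed rates | Power per behaviour at .05 | Power per behaviour at .0167 | n per group for 80% at .0167 (pooled) |
|---|---|---|---|
| 40% vs 50% or 50% vs 60% | 80% | 65% | 517 |
| 20% vs 30% | 89% | 79% | 392 |

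**4. Restriction to baseline non-performers.** The inflation to 1000 covers response and dropout only. If, as an illustration, half of the 384 were not doing a behaviour at baseline (192 per group), power at an unadjusted .05 would be 50% for 40% vs 50% and 62% for 20% vs 30%.

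**The case against.** **An unseen analysis plan may settle this.** Multiplicity rules and a primary time point are often left to it, and the article is a condensed account. That is fair for the method of adjustment. It does not remove the mismatch inside this document between one hypothesis with one power calculation and three parallel outcomes.

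**Testing each behaviour at .05 at every wave is an inference.** This stands. The article says when questionnaires are sent, not that each wave is a separate efficacy test, and .05 appears only in the sample size paragraph. The minimum reading is three comparisons.

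**A reader might infer a false efficacy rate of 30-35% against 5%.** The documents do not support that. It is roughly the rate of any difference in either direction over nine comparisons with low to moderate correlation. A false claim of efficacy must favour the intervention, which about halves the figure and makes 2.5% the benchmark.

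**A reader might also count 18 comparisons by adding the preparatory acts.** The list in Statistical Analysis uses the wording of doing (using, performing), which corresponds to the structural measures. Preparatory acts are not in it.

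**The Discussion speaks of a 10% change, not of a CI excluding 1.** Read as an observed 10-point difference, with 384 per group and a rate near 50%, the standard error is √(0.5/384) = 3.6 points. Ten points is then about 2.8 standard errors: roughly 0.3% per comparison, or 2.5% over nine independent ones. This shows how much depends on the missing rule. With 192 per group the standard error is √(0.5/192) = 5.1 points, ten points is 1.96 standard errors, and the rate returns to 2.5% per comparison.

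**Power for any one success is higher.** With true 10-point effects on all three behaviours, Bonferroni gives 1 − 0.347³ = 96% if independent, and less if correlated. This also stands: the 65% is power per behaviour, not for any one of three.

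**Conclusion.** The point holds in limited form. The article fixes no primary behaviour, time point or success rule, and its sample size covers one comparison. If any nominally favourable interval can carry the claim, the false favourable rate is about 7% for three independent comparisons and about 11-20% for nine, against 2.5% for one. In either direction it is 14% and about 22-37%, against 5%. Even the minimum reading nearly triples the single-test rate.

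The nine-comparison figures assume that every wave is analysed and rest on assumed correlations. The per-behaviour power of about 65% after adjustment depends on the assumed rates that reproduce 384; at 20% vs 30% it is about 80%. Neither is the trial's actual power, because each analysis excludes participants already doing the behaviour at baseline.

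**What to change.** 1. In Statistical Analysis, name the three structural behaviours at one time point as the primary family, for example 5 months, each taken from one named questionnaire item (past-period or current).
2. Apply Holm across the three. Alternatively, state that all three must succeed; each is then tested at .05 without adjustment.
3. Label the other time points and the preparatory acts as secondary.
4. State what the 10% criterion means: an observed difference, or the difference the trial was sized to detect.
5. Restate the power in Sample Size and Allocation at the level used, with the control rate and the expected number of baseline non-performers.

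The cost is wording and a lower stated power. For Holm it is about 65% at the first step for one behaviour at 50% vs 60%, and about 80% at 20% vs 30%. If all three must succeed, it is about 0.8³ = 51% at 80% each, if independent. All these figures are before the baseline restriction.

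The Results section says enrolment is complete and analysis is under way. The choice should therefore be made and dated before results by arm are seen, or disclosed as post hoc.

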### Recruitment of Participants

For the study results to be meaningful, 1000 novice runners need to be enrolled. To enhance enrollment and the possibility to preregister for the study, several strategies will be used, such as social media (Facebook, LinkedIn, and Twitter), newsletters from the RDRA (digital), and the magazine Runner’s World (in print and digital). Preregistration will be possible by filling in a Web-based form on the website of the Dutch Consumer Safety Institute. Preregistration for the study will be advertised on Facebook and Twitter.

Social media has been previously utilized by the research team to recruit runners with close to 1000 participants recruited within 2 weeks. Respondents were recruited via social media, such as Facebook and Twitter, and they were invited to give their opinion on running, running injuries, and injury prevention. As the research team recruited nearly 1000 runners within 2 weeks, they are confident that they will achieve 1000 participants in this study with similar recruitment strategies.

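### The 80% power and 384 per group are set for all participants and are not shown for the baseline non-performers in whom each behaviour is analysed

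*Protocol article*

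**What the plan says.** - **Hypothesis** (Objective and Hypothesis): the intervention is expected to produce a "10% difference in favorable injury-preventive behavior in the intervention group compared with the control group". This is worded for the two groups as a whole.
- **Size** (Sample Size and Allocation): "To achieve 80% power with a significance level of.05", "the sample size calculation revealed that 384 participants per study group are needed in this study". After an 85% response rate and 10% dropout, "a total of 1000 participants will be approached in this study". No other loss is allowed for.
- **Eligibility** (Participants and Recruitment): depends on age, self-rated level and running experience, not on whether a runner already takes preventive measures.
- **Analysis set** (Statistical Analysis): relative risks for a training schedule, strength and technique exercises, and warm-up. For these, "Participants who do not execute a certain injury-preventive measure at study commencement will be selected for analysis", on the ground that most change can be expected there. No comparison of behaviour in the whole groups is described beside it.
- **Further removal** (Running as Usual): control participants who visited the intervention website are left out of the analyses.

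**The concern.** The article states both the sample size and the analysis set, and they describe different groups of people. The 384 per group counts everyone who responds and stays in follow-up. Each of the three analyses uses only those not doing that behaviour at enrolment, so there are three subsets of unknown and probably different size. The control group loses website visitors as well.

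Two things are at stake. A null result for a behaviour could be read as coming from an 80%-powered comparison when nothing in the article shows that. And the stated hypothesis, about the groups as a whole, has no analysis described that matches it: runners who already perform a behaviour, and may lapse or keep it up, never contribute.

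**Working it through.** **Inputs from the article:** power 80%; alpha .05; 384 per group; difference 10%; response 85%; dropout 10%; total 1000.

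**Assumptions, because the article does not give them:** two-sided test; 1:1 allocation; 10% read as 10 percentage points; control uptake p1; share f of participants not doing the behaviour at baseline, shown from 0.3 to 0.9.

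**Step 1: the 384.** With p2 = p1 + 0.10 and p̄ their mean:

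- Unpooled: n = (1.96 + 0.842)² × [p1(1−p1) + p2(1−p2)] / 0.10². At 40% v 50%: 7.849 × 0.49 / 0.01 = 384.6.
- Pooled: n = [1.96√(2p̄(1−p̄)) + 0.842√(p1(1−p1) + p2(1−p2))]² / 0.10². At 40% v 50% this is 387.3, so 388. It gives 384 at control rates of about 38% and 52%, 376 at 35% and 55%, and 392 at 45%.

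So 384 fits control rates of about 35% to 55%. It cannot be pinned to one rate. Other readings fit less well: a one-sided test needs at most 309. A 10% relative difference needs 623 or more at control rates of 50% to 70%, and 329 at 80%.

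**Step 2: the 1000.** 768 / (0.85 × 0.90) = 1004, stated as 1000. In reverse, 1000 × 0.85 × 0.90 / 2 = 382.5 per arm. The two stated losses use up the whole allowance. The gap between 382.5 and 384 is rounding.

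**Step 3: apply the restriction.** Analysed n per arm = 384 × f, before removing any control visitors. Power = Φ{[0.10√n − 1.96√(2p̄(1−p̄))] / √(p1(1−p1) + p2(1−p2))}. Example at f = 0.5, 40% v 50%: n = 192, (1.386 − 1.379) / 0.70 ≈ 0.01, power 50%.

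| f | n per arm | 5→15% | 10→20% | 15→25% | 20→30% | 30→40% | 40→50% |
|---|---|---|---|---|---|---|---|
| 0.9 | 346 | 99% | 96% | 91% | 86% | 79% | 75% |
| 0.8 | 307 | 99% | 94% | 87% | 82% | 74% | 70% |
| 0.7 | 269 | 97% | 90% | 83% | 76% | 68% | 65% |
| 0.5 | 192 | 91% | 79% | 69% | 62% | 54% | 50% |
| 0.3 | 115 | 72% | 57% | 47% | 42% | 36% | 33% |

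A control rate of 50% gives the same figures as 40%; 45% is at most one point lower; 35% and 55% are slightly higher.

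**Step 4: what 80% would need.** For a 10-point difference in the subset, the pooled n per arm is 141 at 5% control uptake, 199 at 10%, 250 at 15%, 294 at 20% and 356 at 30%. Divided by 384, the share of non-performers must be at least about 0.37, 0.52, 0.65, 0.77 and 0.93.

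**Step 5: the 10 points as a whole-group effect arising only in non-performers.** The subset difference is then 10/f points: 12.5 at f = 0.8, 20 at f = 0.5. With n = 384 × f, power was at least 87% in every case computed (f from 0.4 to 0.8, control uptake from 5% to 40%).

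**The case against.** The strongest reply is that lack of power is not proved. Power in the subset turns on the share of non-performers, their uptake without the intervention, and which population the 10% describes. Runners who start as non-performers and are offered nothing may well have low uptake, and Steps 3 to 5 contain many cells above 80%. This stands. A reader might infer that the trial does not have its stated power; the article does not support that flat conclusion. Nor does it support saying that 80% is reached under only one combination of inputs, or that 384 can come only from a control rate of 40% or 50%.

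It does not rescue the stated figure. Each favourable case needs an input the article does not give, and in each of them 384 is not the matching number: fewer are needed at low uptake, and a difference other than 10 points applies in Step 5.

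It can also be said that phrases about increasing or changing behaviour may mean uptake among non-performers, and that selecting on an answer given before randomisation does not break the randomisation. Both are fair. The restriction is a legitimate comparison with a stated reason. The objection here is to the unsupported power statement and the missing link to the whole-group hypothesis. A reader might also infer that the subset result will be presented as the effect in all novice runners; no section says so.

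Finally, the Recruitment of Participants section says "1000 novice runners need to be enrolled", whereas the sample-size section has 1000 approached. If 1000 were enrolled and only dropout applied, 1000 × 0.90 / 2 = 450 per arm would remain, which covers 384 non-performers per arm only if about 85% (384/450) are non-performers. The sample-size section takes both losses off the 1000, so this reading is not the one it states.

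**Conclusion.** The concern holds in this form: the 80% power is stated for all participants and is not shown for the sets in which the behaviours are analysed. The 1000 covers non-response and dropout and nothing else, so any runner already doing a behaviour takes that analysis below 384 per arm, and excluded control visitors take it lower by an amount the article does not give.

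At the control rates that fit 384, power is about 75%, 70%, 65%, 50% and 33% for non-performer shares of 90%, 80%, 70%, 50% and 30%. With low control uptake it can be 80% or more: 91% for 5→15% at a 50% share, 83% for 15→25% at 70%, 82% for 20→30% at 80%. All of this rests on a two-sided test, an absolute 10-point difference and assumed shares.

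**What to change.** 1. State which population the 10% and the 384 refer to, and the control rate assumed.
2. For each behaviour, restate power or expected precision from the number of baseline non-performers in each group. This uses enrolment data only and no outcomes. Enrolment is complete, so recruiting more is not the remedy.
3. Beside the restricted relative risk, report the comparison in all randomised participants, adjusted for baseline performance of that behaviour (for example by modified Poisson or log-binomial regression). Baseline behaviour is collected on everyone (Table 1), and this is the analysis that answers the hypothesis as worded. Because analysis is already under way, label it as a change to the published plan.
4. Describe the restricted relative risk as the effect among runners not doing the behaviour at enrolment, not as the effect in novice runners overall.

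The cost is some wording and one more model per behaviour on data already collected. The downsides are that the whole-group comparison may dilute the effect if change occurs mainly in non-performers, and that the stated power may become less favourable. No correction of 382.5 to 384 is needed.

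### Baseline tests trigger subgroup analyses that cannot correct a chance imbalance; adjusting each relative risk for sex, age and running experience would correct it

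*Protocol article*

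**What the plan says.** All of this is in the Methods of the protocol article.

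- **Allocation** (Sample Size and Allocation): "No restrictions will be imposed for the allocation; simple randomization will be performed", "using a computerized random number generator (the Aselect function in Excel").
- **Baseline comparison** (Statistical Analysis): "To evaluate the success of the randomization, baseline variables will be analyzed for differences between the intervention and control group", with chi-square, t and Mann-Whitney tests named.
- **Consequence of a difference** (Statistical Analysis): "If there are any differences in descriptive characteristics at baseline (eg, differences in sex, age, or running experience), subanalyses for sex, different age categories" and others left open are to be carried out. No threshold, closed list of variables or age cut-points is given.
- **Main analysis** (Statistical Analysis): "Relative risks (RRs) and a 95% CI will be used to analyze behavioral change according to the intention-to-treat analyses", for three behaviours. "Participants who do not execute a certain injury-preventive measure at study commencement will be selected for analysis", so each behaviour is analysed among those not already doing it.

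Table 1 (Procedures) lists 12 topics in the enrolment questionnaire, among them sex, age and running experience.

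**The concern.** Three features of the stated rule do not fit together.

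1. **The tests do not answer their question.** If the random number generator was used as described, the null hypothesis of each baseline test is true by design. A small p-value is then a chance event and says little about whether randomisation worked.
2. **The remedy does not match the problem.** A subgroup analysis asks whether the effect differs between, say, men and women. It does not remove an imbalance in sex from the overall relative risk. The headline estimate keeps the imbalance that prompted the extra work.
3. **The choice of extra analyses is driven by the data.** A variable with little bearing on the outcome can trigger a subanalysis, while a prognostic variable with a smaller difference is passed over.

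At stake are a set of underpowered subgroup results whose existence depends on chance, and a main estimate left uncorrected in the very trials where an imbalance is noticed.

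**Working it through.** **Inputs from the document:** 384 per group, 80% power, significance level .05, 10% difference, 85% response, 10% dropout, 1000 approached, 12 enrolment topics in Table 1, three variables named in the trigger sentence.

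**Assumptions, because the document is silent:** two-sided testing; 10% read as 10 percentage points; a control rate (varied below); a 0.05 threshold for a baseline difference; independent baseline tests.

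**1. The plan's own sample size.** With 50% against 60%, mean 0.55:

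- Pooled formula: (1.96·√(2·0.55·0.45) + 0.8416·√(0.50·0.50 + 0.60·0.40))² / 0.10² = 388.
- Unpooled formula: (1.96 + 0.8416)² · 0.49 / 0.10² = 384.6, so 385.
- Total: 768 / (0.85 · 0.90) = 1004, against 1000 stated.

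The stated 384 fits a control rate of about 40% to 50%. At 30% the pooled formula gives 356, at 20% 294 and at 10% 199. The sample size itself is not disputed here.

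**2. How often the trigger fires by chance.** P(at least one) = 1 − 0.95^k.

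| Variables tested | k | Chance of at least one difference |
|---|---|---|
| Sex, age, running experience | 3 | 14% |
| All Table 1 topics | 12 | 46% |

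Positive correlation between variables, such as running experience and level of running, would lower these figures.

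**3. Power in a half-size subgroup.** With 384 / 2 = 192 per arm, power = Φ((d − 1.96·SE₀)/SE₁), where SE₀ uses the pooled rate and SE₁ the separate rates. For 50% against 60%: SE₀ = √(0.2475·2/192) = 0.0508, SE₁ = √(0.49/192) = 0.0505, and power = 50%.

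| Assumed control rate | Power for +10 points, 384 per arm | 192 per arm |
|---|---|---|
| 50% | 80% | 50% |
| 30% | 83% | 54% |
| 20% | 89% | 62% |
| 10% | 97% | 79% |

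These take 384 as the analysed number per arm. If 384 also has to cover baseline performers, the restriction to non-performers lowers every entry.

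**4. What adjustment does and subgrouping does not.** A simulation (200,000 trials per setting, 384 per arm) used an invented binary covariate with 50% prevalence. The outcome was compared as a risk difference, unadjusted and standardised over the covariate. *Flagged* means that the baseline test of the covariate was significant at 0.05.

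| | Outcome 40% vs 60% by covariate level | Outcome 30% vs 70% |
|---|---|---|
| Type I error, all trials, unadjusted | 4.6% | 4.8% |
| Type I error, flagged trials, unadjusted | 6.6% | 13.1% |
| Type I error, flagged trials, adjusted | 5.2% | 5.1% |
| Bias when the imbalance favours intervention, unadjusted | +1.7 points | +3.5 points |
| Same, adjusted | about 0 | about 0 |
| Power for +10 points, unadjusted → adjusted | 80.1% → 81.6% | 80.0% → 86.4% |

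Testing the two covariate subgroups separately gave about a 10% chance of at least one false positive under the null (1 − 0.95² = 9.75%). The covariates are illustrative; the document gives no prognostic strength for sex, age or experience.

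**The case against.** **The main analysis is not affected.** This stands. The relative risks, the three behaviours and the restriction to non-performers are fixed whatever the baseline tests show, and nothing lets a subanalysis replace them. A reader might infer that the main result is invalid or that its population is picked by chance. The text does not support that: only the extra subanalyses are conditional, and an unadjusted relative risk keeps its nominal error rate over repeated trials.

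**Baseline data are used.** This stands in part. Baseline behaviour enters through the restriction to non-performers, so it would be wrong to say that baseline information is ignored. Within each such set the matching behaviour is constant and cannot serve as a covariate. Sex, age and running experience remain available.

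**No p-value rule is written.** Correct. A 0.05 trigger is inferred from the tests named in the preceding paragraph. An undefined trigger leaves more discretion, not less.

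**A check on randomisation has some use.** One researcher carries out every randomisation step in Excel, so checking execution is not pointless. Also, the Running as Usual section excludes control participants who visited the website, so differences in the analysed set need not be pure chance. Neither point rescues the rule: splitting the sample corrects neither kind of difference.

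**An unseen analysis plan may hold the detail.** A missing covariate list alone would be no finding. The criticism here is of a rule that the article states.

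**Conclusion.** The concern holds as a badly chosen rule for handling baseline differences. It is a should-fix matter and not an error in the main result.

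Baseline tests should not trigger analyses, and subgroup analyses do not repair an imbalance in the overall relative risk. By chance alone the trigger would fire in about 14% of trials if three variables are examined and up to 46% if all 12 topics are, assuming a 0.05 threshold and independence. A half-size subgroup has about 50% power for a 10-point difference at an assumed 50% control rate, rising to 79% at 10%, before the restriction to non-performers.

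The size of the benefit from adjustment cannot be fixed from the document. The gains of 1.5 and 6.4 points in power belong to invented covariates and show direction only.

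**What to change.** - **Baseline table:** report it descriptively, without between-group tests, and remove the sentence that makes subanalyses depend on differences.
- **Main model:** estimate each relative risk by modified Poisson regression with robust standard errors, or log-binomial regression, adjusted for sex, age and running experience whatever the baseline table shows. Give the unadjusted relative risk in support.
- **Baseline behaviour:** do not enter the matching behaviour as a covariate while the restriction to non-performers stands. It becomes usable only if all participants are analysed, which would be a separate change to the plan.
- **Subgroups:** name any in advance, with cut-points, and assess them by an interaction term.
- **Timing:** the Results section says that analysis is under way. Set these choices before between-group outcomes are examined. If that is no longer possible, label the adjusted model and any triggered subanalyses as not pre-specified.

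**Cost:** wording in the analysis section and a standard regression model. The three covariates are already in the enrolment questionnaire, so no new data are needed.
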